## Abstract

**Background:**

Traditional treatment alone might not effectively control the severity of attention deficit hyperactivity disorder (ADHD) symptoms. Transcranial pulse stimulation (TPS) is a non-invasive brain stimulation (NIBS) technology used on older adults with mild neurocognitive disorders and adults with major depressive disorder. However, there has been no study conducted on young adolescents with ADHD. This will be the first nationwide study evaluating the efficacy and safety of TPS in the treatment of ADHD among young adolescents in Hong Kong.

**Methods:**

This study proposes a double-blinded, randomized, sham-controlled trial including TPS as an intervention group and a sham TPS group. Both groups will be measured at baseline (T1), immediately after the intervention (T2), and at the 1-month (T3) and 3-month follow-ups (T4).

**Recruitment:**

A total of 30 subjects aged between 12 and 17 years, diagnosed with attention deficit hyperactivity disorder (ADHD), will be recruited in this study. All subjects will be computer randomized into either the intervention group or the sham TPS group on a 1:1 ratio.

**Intervention:**

All subjects in each group will have to undertake functional MRI (fMRI) before and after six 30-min TPS sessions, which will be completed in 2 weeks' time.

**Outcomes:**

Baseline measurements and post-TPS evaluation of the ADHD symptoms and executive functions will also be conducted on all participants. The 1- and 3-month follow-up periods will be used to assess the long-term sustainability of the TPS intervention. For statistical analysis, ANOVA with repeated measures will be used to analyze data. Missing data were managed by multiple imputations. The level of significance will be set to *p* < 0.05.

**Significance of the study:**

Results emerging from this study will generate new knowledge to ascertain whether TPS can be used as a top-on treatment for ADHD.

**Clinical trial registration:**

clinicaltrails.gov, identifier: NCT05422274.

## Introduction

Local epidemiological data suggest that attention deficit hyperactivity disorder (AD/HD) affects ~6% of children, with a male preponderance of around 2 boys to 1 girl being affected (1). The prevalence in adults is around 2.5% (2). Clinical features of ADHD are characterized by persistent symptoms of inattention and/or hyperactivity/impulsivity (3) that emerge in childhood (4). These symptoms may persist into adulthood, leading to poor life outcomes, and affecting employment and interpersonal relationships (5). ADHD may affect all aspects of an individual's life and has a negative detrimental impact on family members (6). The neurobiological mechanism of ADHD may be attributed to the dopaminergic imbalance in the forebrain and basal ganglia. The prefrontal cortex, anterior cingulate, insula, amygdala, and cerebellum are also linked to ADHD pathophysiology (7). Typical ADHD treatments include pharmacotherapy, stimulant medications (e.g., methylphenidate; amphetamine), and non-stimulant medications (e.g., atomoxetine) (8) targeting dopaminergic and noradrenergic systems in the frontal cortex and dopaminergic system in the basal ganglia. These medications are effective and safe for the majority of patients; however, 20% of patients do not tolerate these medications or fail to respond (9). Although these medications can significantly improve ADHD symptoms and life outcomes, long-term medication compliance is necessary to sustain the treatment efficacy (10). Drug dosages also need to be individually monitored to minimize adverse effects while maintaining efficacy (8). Whether the long-term risk of taking medications outweighs the benefits in patients with ADHD remains debatable. Although mindfulness-based cognitive therapy (MBCT) has recently been demonstrated as an effective psychosocial intervention (11), the long-term sustainability of the benefits of these psychosocial interventions on ADHD is yet to be confirmed. Pharmacotherapy is not considered as a monotherapy for more than 50% of adult ADHD, (12, 13) and a combination of cognitive behavioral therapy (CBT) and medication produces broader improvements in executive functions in ADHD than CBT alone.

## Neuromodulation and non-invasive brain stimulation (NIBS)

Attempts to design interventions that could directly modulate brain function have received increasing interest with the advent of technology capable of delivering highly focal and tailored modulation of special brain circuit. Non-invasive brain stimulation (NIBS), such as repeated transcranial magnetic stimulation (rTMS) and transcranial direct current stimulation (tDCS), is widely applied to re-balance neural activity at the circuitry level to normalize functions and behavior. Nowadays, these NIBS techniques are being used diagnostically and therapeutically in different types of neurodegenerative diseases (e.g., Alzheimer's disease and Parkinson's disease) (14), pediatric epilepsy (15), neuropsychiatric disorders (e.g., ADHD, major depressive disorder, and substance use disorder) (16), and neurodevelopmental disorders (e.g., autism) (17). A recent systematic review (18) of neurotherapeutics on ADHD presented meta-analytic evidence that EEG-neurofeedback showed small/medium effects compared to non-active controls in randomized controlled trials. Trials evaluating rTMS or tDCS, however, have yielded more mixed outcomes. Nevertheless, rTMS showed inconsistent findings on improving cognition or symptoms in ADHD, while tDCS studies that targeted the dorsolateral prefrontal cortex (DLPFC) showed small effects on cognitive improvements in ADHD. The key findings targeted on specific age groups (e.g., children, adolescents, and adults) of people with ADHD are summarized below (Table 1).

**Table 1 T1:** Findings of non-invasive brain stimulation (NIBS) studies on ADHD.

**References**	** *N* **	**Age**	**Design**	**Intervention**	**Treatment region**	**Results**
Allenby et al. (4)	37	18–65	Double-blind, sham-controlled randomized controlled trials (RCT)	3 tDCS sessions	Left DLPFC	tDCS improved impulsivity symptoms
Cao et al. (19)	64	6–13	3-armed RCT rTMS (*n* = 20); ATX (*n* = 19); rTMS + ATX (*n* = 21) *ATX = Atomoxetine	6-week rTMS	Right DLPFC	rTMS + ATX group improved significantly in inattention and hyperactivity/impulsiveness at post-treatment (*p* < 0.05). All groups showed improvements in clinical/cognitive measures.
McGough et al. (20)	62	8–12	Double-blind, sham-controlled RCT	4 weeks trigeminal nerve Stimulation (TNS)	Right frontal lobe and frontal midline	Significant reduction of ADHD-RS score (*p* = 0.005) and CGI score on active TNS group (*p* = 0.003) compared to sham TNS group
Soff et al. (21)	15	12–16	Double-blind RCT	5 tDCS	Left DLPFC	Significant reduction of hyperactivity and inattention (*P* < 0.05) but no effect on impulsivity
Paz et al. (22)	22	12–16	Single-blind RCT	20 rTMS	Bilateral DLPFC	No effect on clinical/cognitive outcomes (*p* > 0.05)
Westwood et al. (23)	50	10–18	Double-blind, sham-controlled RCT	15 tDCS	rIFC	No significant improvement in core ADHD symptoms (*p* > 0.05)
Leffa et al. (24)	64	18–60	Double-blind, parallel, sham-controlled RCT	20 tDCs	Anodal-right and cathodal-left prefrontal	Mean inattention score was 18.88 (SD 5.79) in the active tDCS group compared with 23.63 (SD 3.97) in the sham tDCS. Significant treatment by time intervention evaluated by clinician-administered version of the adult ADHD self-report scale (β interaction: −3.18, *P* < 0.001).
Cosmo et al. (25)	60	18–65	Double-blind, sham-controlled RCT	1 tDCS session	Left DLPFC	No significant differences in ADHD symptoms between the tDCS and sham group

In summary, with the exception of trigeminal nerve stimulation (TNS), which has proven a safe and effective intervention for ADHD, other NIBS studies such as EEG-neurofeedback and rTMS/tDCS across different age groups have yielded inconsistent results in ADHD. Almost all NIBS studies primarily focused on left/right/bilateral DLPFC in ADHD. Stimulation targeting the right inferior frontal cortex (rIFC) was shown to be ineffective (26). Since ADHD is increasingly prevalent in Hong Kong, and thus, there is a pressing need to evaluate the efficacy of the latest NIBS technology (such as transcranial pulse stimulation, TPS), not only would such research generate new neuroscientific evidence but would also ascertain whether TPS may be an effective adjunct treatment in ADHD to reduce disease burden and psychiatric morbidity [e.g., mood disorders/anxiety disorders (27), eating disorders, and substance-related disorders (28)] in Hong Kong.

## Mechanisms of TPS

Transcranial pulse stimulation uses repetitive single ultrashort pulses in the ultrasound frequency range to stimulate the brain. With a neuro-navigation device, TPS can target the human brain in a highly focal and precise manner (29). TPS differs from tDCS and rTMS, as these use direct or induced electric current. Using electric currents to stimulate the brain may be limited by the problem of conductivity (30) and failure to reach deep brain regions (31). TPS, however, uses low-intensity focused ultrasound which provides good spatial precision and resolution to non-invasively modulate subcortical areas, despite the problem of skull attenuation (32, 33). By using lower ultrasound frequencies, TPS can stimulate deep cerebral regions, reaching as far as 8 cm into the brain. In other words, TPS can improve skull penetration in the human brain and improve treatment outcomes (29). The biological mechanism of TPS is mechanotransduction. TPS can stimulate vascular growth factors (VEGF) (34, 35) and brain-derived neurotrophic factor (BDNF) (36), improve cerebral blood flow, and promote angiogenesis and nerve regeneration. The ultrashort ultrasound pulse can enhance cell proliferation and differentiation in cultured neural stem cells, and this TPS may play an important role in the repair of brain function in CNS diseases (37).

## Existing research on transcranial pulse stimulation

Ultrasound for the brain is a revolutionary therapeutic treatment approach in patients with neuropsychiatric symptoms (38). Since TPS is a relatively new NIBS technology, only two studies have so far been conducted on the disease population. The first study comprised of 35 Austrian older adults with Alzheimer's disease (AD) who were treated with global brain stimulation in three TPS sessions per week (6,000 pulses each) for 2–4 weeks, with results showing significant improvement in the Consortium to Establish a Registry for Alzheimer's Disease (CERAD) score immediately after intervention and at 1 and 3 months after the intervention. Results from fMRI also showed significantly increased connectivity within the memory network (29). Participants' depressive symptoms were also significantly improved, as measured by the Geriatric Depression Scale (GDS) (*p* = 0.005) and the Beck Depression Inventory (BDI) (*p* < 0.0001) at 1 and 3 months post-stimulation follow-ups compared with the baseline scores (29). The second TPS study was executed by the principal investigator (PI) ([name]) of this proposed study. The study evaluated TPS in people with major depressive disorder (MDD) in an open-label pilot randomized controlled trial (RCT) using waitlist controls (WC). A total of 30 subjects (18–51 years) were administered six TPS sessions over 2 weeks (total TPS pulse: 1,800–2,400, 2.5–3.0 Hz). Results showed significant improvement in the depression severity in the verum TPS group compared to WC (*p* = 0.02), and the effect size was very large (Cohen's *d* = −0.9) (39). However, both Beisteiner et al. (29) and Cheung et al.'s (39) studies were uncontrolled studies or open-label RCTs without a sham control group. Placebo effects have to be considered when interpreting results. Since then, there has been no further attempt to use TPS on neurodevelopmental disorders in children or young adolescents in Hong Kong and nationwide. The impetus of our proposed research is to fill this research gap, which could be critical for the management of ADHD.

### Treatment region

In this trial, we will target the left dorsal lateral prefrontal cortex (DLPFC). The selected brain region is based on previous tDCS research that left and right DLPFCs (40) are primarily the brain treatment regions for ADHD and that stimulation of left DLPFC, specifically, can effectively improve inattention and hyperactivity (4, 21).

## Objectives

The aim of this study is (1) to evaluate the efficacy and safety of TPS on young adolescents (12–17 years) with ADHD in Hong Kong; (2) to examine the association between TPS and ADHD core symptom severity, executive function, inattention, hyperactivity, impulsivity, and oppositional defiance; and (3) to examine the brain functional connectivity changes immediately after the 2-week TPS treatment *via* neuroimaging.

## Hypotheses

### Primary hypothesis

Participants in the verum TPS group will have a 30% reduction in the Swanson, Nolan, and Pelham Rating Scale (SNAP IV score) (i.e., attention deficit, hyperactivity impulse, and oppositional defiance) after 2 weeks of TPS treatment compared with the sham TPS group and be maintained at the 1- and 3-month follow-ups.

### Secondary hypotheses

Participants in the verum TPS group or the sham TPS group will have < 5% somatic discomfort during the 2-week TPS intervention on young adolescents with ADHD.Participants in the verum TPS group will have a 30% improvement in ADHD symptoms and behavior compared with the sham TPS group after 2 weeks of TPS treatment and be maintained at the 1- and 3-month follow-ups.Participants in the verum TPS group will have a 30% improvement in executive function after 2 weeks of TPS treatment compared with the sham TPS group and be maintained at the 1- and 3-month follow-ups.Participants in the verum TPS group will have a 30% improvement in both attention deficit and reduction in hyperactivity and impulsivity after 2 weeks of TPS treatment compared with the sham TPS group, and be maintained at the 1- and 3-month follow-ups.Participants in the verum TPS group will have more brain connectivity changes after 2 weeks of TPS compared with the sham TPS group and be maintained at the 1- and 3-month follow-ups.

## Trial design

This proposed study is a two-armed, randomized, double-blind, sham-controlled trial evaluating the efficacy and safety of a 2-week TPS treatment on young adolescents with ADHD. The trial design complies with the Consolidated Standards of Reporting Trials (CONSORT) statement (41). Participants will be randomly allocated into the verum TPS group or sham TPS group. All the participants' parents will be informed about the randomization procedures and that they have a 50% chance of receiving the verum TPS or the sham TPS. This study will be conducted in accordance with the Declaration of Helsinki (42). Both groups will be measured at baseline (T1), immediately after the 2-week intervention (T2), and at 1- and 3-month follow-ups (T3) (43) (Figure 1).

**Figure 1 F1:**
[figure not shown]
Flow diagram for subjects' enrollment, randomization, allocation, and follow-up.

## Methods

### Subjects

Participants will be recruited *via* a mass email invitation attached with a QR code poster that will be delivered *via* members of the Hong Kong Association for ADHD, CUHK, and HKU. A QR code flier will also be flagged up in communal areas on campus. The recruitment period will span 2 months. All participants will require parental written consent for TPS treatment and neuroimaging. Both participants and their parents will be informed that this study involves random allocation into either a sham or treatment group, and the possible side effects of TPS will be clearly stated in the information sheet.

### Inclusion criteria

The inclusion criteria are as follows: (1) those who have a confirmed diagnosis of ADHD according to the 5th edition of the Diagnostic and Statistical Manual of Mental Disorders (DSM-5) of the American Psychiatric Association; (2) those with Chinese ethnicity, aged 12–17 years, with no co-morbidity of other mental disorders (e.g., intellectual disability disorders) or organic brain diseases that affect cognitive functions; (3) those who have no severe systemic diseases including heart, liver, lung, and kidney diseases; (4) those who have an IQ of >80 by Stanford–Binet Intelligence Scale, 5th Edition (SB-5); and (5) those who have written consent from parents.

### Exclusion criteria

The exclusion criteria are as follows: (1) SNAP IV score < 1; (2) those who had not taken ADHD medication in the previous 2–4 weeks; (3) those who had been treated with TMS/rTMS/tDCS or electroconvulsive therapy in the previous 12 months; (4) those who had taken monoamine oxidase inhibitors in the previous 14 days; (5) those who have a history of epilepsy, brain trauma, brain surgery/brain tumor, brain aneurysm, or other concomitant unstable major medical conditions like hemophilia or other blood clotting disorders or thrombosis; (6) those who have significant communicative impairments; (7) those who have metal implants in the brain treatment region or artificial cardiac pacemaker *in situ*; (8) those who had had corticosteroid treatment within the previous 6 weeks before the first TPS treatment; and (9) those who have a history of micro-cavernomas.

### Sample size

To the best of our knowledge, there is no interventional study evaluating the efficacy of TPS on ADHD. Based on our previous open-label pilot RCT (39) evaluating TPS in adults with major depressive disorder that showed a large effect size (d = 0.91), we hypothesize a large effect of TPS in this study. We used G^*^power version 3.1.9.4 to calculate the target sample size. With a statistical power of 95% and a statistical significance level of 0.05 to detect a medium between-groups effect size (d) of 0.91 with four measurement time points, each group will require 15 subjects. A total sample of 30 is required in this trial. The attrition rate in our pilot MDD trial was 0%. We expect that the attrition rate in this ADHD trial would be < 5%. Subjects dropping out of the 2-week intervention period will be replaced by another enrolled subject in this pilot study.

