### Statistical analyses

All statistical analyses will be performed using the statistical software R for Windows (R version 4.1.0). Means and standard deviations (SD) for the continuous variables will be presented, while numbers and percentages for the categorical variables will be shown. A *p*-value of < 0.05 is considered statistically significant. Sociodemographic differences between the TPS group and the sham TPS group will be analyzed using the Chi-square test and *t*-test. If there are significant differences between sociodemographic factors, covariates will be considered confounding variables in the analyses. The normality of the primary outcome (SNAP-IV) scores will be tested by the Shapiro–Wilk test for each combination of factor levels (group and time). *T*-test will be used to test the baseline difference. A linear mixed model will be used to test the group (between-subject factor), time (within-subject factor), and group × time interaction effects of the SNAP-IV score between the TPS group and the sham TPS group. *Post-hoc* comparisons between groups and time points will be conducted using a *t*-test with Bonferroni correction. The normality of the secondary outcome scores will be tested by the Shapiro–Wilk test for each time point. For normally distributed outcomes, a linear mixed model will be used to determine whether the outcome scores are significantly different between the pre- and post-tests. For outcome scores that deviate grossly from normality, a non-parametric Friedman test will be used to test the mean difference. A Cohen's *d* effect size for each outcome will be calculated, where *d* = 0.2, 0.5, and 0.8 correspond to small, medium, and large effect sizes (54). Missing data will be managed by multiple imputations (55). For the neurological rs-fMRI data, a longitudinal voxel-based morphometry (VBM) will be used to examine whether TPS produces local changes in gray matter. Specifically, relative local increases and decreases between pre- and post-intervention scans will be compared within and between study groups. The diffusion MR data will be analyzed using the diffusion tensor model (56). Two standard diffusion indices will then be obtained: the apparent diffusion coefficient and the fractional anisotropy. Pre- and post-treatment DTI scans will permit the assessment of changes in axial diffusivity, with lower values being interpreted as the structural enhancement of white matter.

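### The stated 95% power for 15 per group at d = 0.91 is not delivered by the planned analyses under ordinary assumptions

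*Protocol article*

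**What the plan says.** The Sample size section takes its effect from an earlier open-label pilot "evaluating TPS in adults with major depressive disorder that showed a large effect size (d = 0.91)" and hypothesises a large effect here too. It then gives the inputs: "With a statistical power of 95% and a statistical significance level of 0.05", used "to detect a medium between-groups effect size (d) of 0.91 with four measurement time points, each group will require 15 subjects". The total is 30, from G*Power 3.1.9.4. The test family, the sidedness, the correlation between visits and the conversion of d are not given.

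The primary hypothesis is a verum–sham difference in SNAP-IV after 2 weeks, maintained at 1 and 3 months. The Statistical analyses section tests group, time and group × time in a linear mixed model, followed by Bonferroni-corrected t-tests between groups and time points. The same section says that d values of 0.2, 0.5 and 0.8 "correspond to small, medium, and large effect sizes".

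Of the two earlier TPS studies, including the one that supplied 0.91, the section on existing TPS research says: "Placebo effects have to be considered when interpreting results".

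**The concern.** A between-groups d of 0.91 with 15 per arm looks too small for 95% power: a plain two-group comparison would need more than twice as many. The mention of four time points might make up the difference, but only under assumptions that are not printed. What is at stake is how a null result would be read. A stated 95% implies a 5% risk of missing the assumed effect. If the planned tests carry a much larger risk, a non-significant result would be taken as stronger evidence against TPS than it is. The effect size adds to this, because it comes from a waitlist comparison and this trial has a sham arm.

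**Working it through.** **Inputs.** From the Sample size section: d = 0.91, n = 15 per arm (N = 30), α = 0.05, m = 4 visits. Assumed here: two-sided tests, equal variances, and one common correlation ρ between visits. The protocol gives no ρ, so 0.3, 0.5 and 0.7 are shown.

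**1. Trying to reproduce 15 per group**

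- *Two-sample t-test.* Noncentrality = d·√(n/2) = 0.91 × √7.5 = 2.49 on 28 df. Power is 67.2% (78.4% one-sided). For 95% it needs 33 per arm (27 one-sided), or d of about 1.37 with 15 per arm. Not reproduced.
- *Repeated measures, between factors.* f = d/2 = 0.455 and λ = f²·N·m/(1 + 3ρ) = 24.84/(1 + 3ρ), on 1 and 28 df. Power is 93.7%, 86.1% and 78.0% at ρ = 0.3, 0.5 and 0.7. At ρ = 0.5, 95% needs N = 42. N = 30 reaches 95% only if ρ is 0.26 or less. This routine also treats the 0.91 SD gap as present at all four visits, including T1.
- *Within–between interaction, f = 0.455, ρ = 0.5.* λ = f²·N·m/(1 − ρ). The required N is 12, not 30.
- *Interaction, with f = 0.455 read as a partial interaction effect.* λ = f²·N·(m − 1) = 0.2070 × 30 × 3 = 18.63 on 3 and 84 df. Power is 95.7%, so N = 30 is reproduced. With N − 2 in place of N, power is 94.3% and N = 31.

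The printed N can therefore be reached, but the article does not say by which route.

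**2. Power of the planned tests when the effect starts after T1**

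Take the verum–sham difference as 0 at T1 and 0.91 SD at T2, T3 and T4.

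- Group × time: λ = (n/2)·0.75·d²/(1 − ρ) = 4.658/(1 − ρ), on 3 and 84 df.
- Group main effect: the mean difference over four visits is 0.75 × 0.91 = 0.6825, so λ = (n/2)·0.6825²·4/(1 + 3ρ) = 13.97/(1 + 3ρ), on 1 and 28 df.
- Baseline-adjusted T2: noncentrality = 0.91·√(7.5/(1 − ρ²)), on 27 df.
- Baseline-adjusted average of T2–T4: noncentrality = 0.91·√(7.5/v), with v = (1 + 2ρ)/3 − ρ², on 27 df.

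| Test, N = 30, d = 0.91 | ρ = 0.3 | ρ = 0.5 | ρ = 0.7 |
|---|---|---|---|
| Group × time | 54% | 71% | 91% |
| Group main effect | 74% | 63% | 54% |
| T2 only, unadjusted | 67% | 67% | 67% |
| T2 only, baseline-adjusted | 71% | 79% | 92% |
| T2–T4 average, baseline-adjusted | 95% | 96% | 99% |

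With Bonferroni over three post-baseline visits (an assumed number), the unadjusted T2 test has 49%.

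**3. What the partial-effect route implies.** Setting 4.658/(1 − ρ) = 18.63 gives 1 − ρ = 0.25, so ρ = 0.75. Read in terms of this design, that route needs a correlation of about 0.75, whereas the between-factors route needs 0.26 or less.

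**4. A smaller effect.** At d = 0.5 the unadjusted T2 test has noncentrality 0.5 × √7.5 = 1.37 and power 26%.

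**The case against.** The strongest reply is that the trial is sized for four visits and a mixed model, so a single-visit figure drops a stated input. That stands: 67% is correct for one unadjusted visit, but it is not the power of the planned model. A reader might infer that 95% is a proven arithmetic error and that the true power is 67%. The document supports neither inference. Two G*Power routes give N = 30. A baseline-adjusted average over T2–T4 also has about 95% or more at essentially any correlation (lowest value 94.97%, at ρ = 1/3), with no gap at T1.

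These routes show that 95% is attainable; they do not show that the plan attains it. The between-factors route assumes a 0.91 SD difference before treatment, although allocation is randomised and balanced on SNAP-IV. The partial-effect route puts a between-groups d in the place of a different quantity. The adjusted average is a sound contrast, but the Statistical analyses section does not state it.

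It can also be said that a condensed article may leave the test and the correlation to a fuller document. That is fair, and their absence alone is not the point. The point is an unqualified 95% printed beside an analysis that does not generally deliver it. The source of the effect size and the pilot status are disclosed, so doubt about whether 0.91 carries over is a judgement on an assumption, not a miscalculation.

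**Conclusion.** The point holds in this form: with N = 30 and d = 0.91, the model effects described in the article fall short of 95% when the groups start equal and separate after T1. Power is 54–91% for group × time and 54–74% for the group main effect over correlations of 0.3 to 0.7. The implied risk of missing the assumed effect is then about 9–46%, not 5%. These figures rest on two-sided tests, equal variances, equal correlation between visits and a constant difference at T2–T4; the correlations are assumptions.

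Separately, 0.91 is called medium directly after a large effect is hypothesised, although the article's own scale puts large at 0.8. That is a wording slip. The 0.91 also comes from a waitlist comparison open to placebo effects, which a sham arm is meant to remove, so the effect in this trial could be smaller and power lower.

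**What to change.** Keep N = 30 and reword the Sample size paragraph in one of two ways.

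1. Name the primary test and replace the unqualified 95% with its power, stating the assumed correlation and a range. For group × time: 54%, 71% and 91% at ρ = 0.3, 0.5 and 0.7.
2. Name the baseline-adjusted verum–sham difference averaged over T2–T4 as the primary contrast, state it in the Statistical analyses section too, and give its power as about 95–99% at d = 0.91 for ρ = 0.3–0.7. This choice should be fixed before anyone sees outcomes by arm.

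In either case, delete the word medium, say that 0.91 comes from an open-label waitlist trial in adult depression, and add power at a smaller effect (26% for the unadjusted T2 test at d = 0.5, or the matching figure for the chosen test). The cost is one paragraph, plus a sentence in the analysis section under the second option. No extra participants are needed. The downside is that the stated power becomes less favourable, except at d = 0.91 under the second option.

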### Randomization, allocation, and masking

All consenting participants will be listed in alphabetical order according to their surnames, and each participant will be assigned a unique identifier. An independent statistician ([name]) will use a computer-generated list of random numbers (www.random.org) to ensure the concealment of randomization. Randomization will be conducted by an independent statistician off-site using a stochastic minimization program to balance the gender, age, and SNAP-IV scores of the participants. Block randomization with blocks of 10 (total: 3 blocks) will be used to allocate treatment groups. Participants from each block will be randomly assigned to the verum TPS groups or the sham TPS groups on a 1:1 ratio. To avoid information flow, participants/parents and research associates will be blinded to the group allocation to minimize potential contamination of the effects of TPS or subject bias. The interventionist will not be involved in data collection or pre- and post-TPS measurements. Outcome measurements will be conducted by a research associate who is not involved in the group allocation. Participants and their parents will be asked to guess the grouping (verum TPS vs. sham TPS) in the last TPS session to determine the probability of guessing the group allocation correctly in the subject blinding (44).

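### Replacing subjects who drop out during the two treatment weeks moves the comparison towards treatment completers, and the randomisation as described has no place for a replacement

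*Protocol article*

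**What the plan says.** The Sample size section sets the target ("A total sample of 30 is required in this trial"), expects attrition below 5%, and then gives the rule: "Subjects dropping out of the 2-week intervention period will be replaced by another enrolled subject in this pilot study".

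The section on randomisation, allocation and masking says: "Block randomization with blocks of 10 (total: 3 blocks) will be used to allocate treatment groups". It also describes off-site allocation by an independent statistician "using a stochastic minimization program to balance the gender, age, and SNAP-IV scores of the participants". It does not say how a replacement is allocated.

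The Statistical analyses section plans a linear mixed model for SNAP-IV and adds: "Missing data will be managed by multiple imputations".

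The first secondary hypothesis sets somatic discomfort below 5% over the same two treatment weeks to which the replacement rule applies.

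**The concern.** Randomisation protects the comparison only while the groups compared are the groups randomised. A subject who leaves during treatment may do so because of discomfort or lack of benefit, and these reasons may differ between verum and sham. Putting someone else in that place removes the subject for a reason that arose after allocation.

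Three consequences follow.

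- **Efficacy.** If dropout is related to outcome and differs by arm, the SNAP-IV comparison can be biased in either direction.
- **Allocation.** A replacement put into the vacated arm is not randomly allocated. A replacement allocated afresh may land in the other arm and so not replace the subject lost.
- **Tolerability.** If dropouts are not counted, the observed discomfort rate can fall, and at this sample size one subject can decide whether it is below 5%.

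The rule also leaves the earliest dropouts to substitution, although the plan already has a method for missing scores.

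**Working it through.** **1. Allocation slots.** From the randomisation section: 3 blocks × 10 = 30. From the Sample size section: 15 per group × 2 = 30. The two agree exactly, so any replacement is a 31st or later subject.

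**2. The planned sample size.** The plan gives 95% power, alpha 0.05, d = 0.91 and four time points, but not the test or the within-subject correlation ρ. With f = 0.91/2 = 0.455 and m = 4, a repeated-measures between-group test has noncentrality f²·N·m/[1 + (m − 1)ρ]. It needs N = 28 at ρ = 0.2 and N = 32 at ρ = 0.3. A total of 30 therefore fits only an unstated ρ between these values. On the interaction test, 24 suffice at ρ = 0 and fewer as ρ rises. This does not decide the present point.

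**3. How often the rule might be used.** Assume a dropout probability of 5%, the upper end of the stated expectation, all of it within the two treatment weeks.

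- P(at least 1 of 30) = 1 − 0.95³⁰ = 79%
- P(at least 2 of 30) = 1 − 0.95³⁰ − 30 × 0.05 × 0.95²⁹ = 45%

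These are upper figures: the expectation is below 5%, and some attrition may fall in follow-up.

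**4. Illustrative worst case.** Assumptions: no true effect, standard normal outcomes, 15 per arm, two-sided t-test at 0.05. The k worst verum outcomes are removed and replaced by fresh random subjects, with no loss in sham. The expected shift is the sum of the k worst outcomes divided by 15. Results from 40,000 simulated trials:

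| Verum subjects replaced | Mean shift favouring TPS (SD) | False significance favouring TPS |
|---|---|---|
| 0 | 0.00 | 2.4% |
| 1 | 0.12 | 5.5% |
| 2 | 0.20 | 9.0% |
| 3 | 0.26 | 12.5% |

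One replacement is 1/30 = 3.3% of the trial. Two are 6.7% and three are 10%, both above the stated expectation as realised rates. By symmetry, the same loss in the sham arm gives the same shift against TPS.

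**5. Milder case.** Assume 5% dropout in verum only, with correlation r = 0.5 between the tendency to drop out and the outcome, and all 15 places filled by completers. The shift is r·φ(z₀.₉₅)/0.95 = 0.5 × 0.103/0.95 = 0.05 SD. Simulation gives 0.05 SD and 3.4% false significance favouring TPS.

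**6. Discomfort threshold.** Read the 5% as a proportion of subjects.

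- Per arm: 1/15 = 6.7% is above 5%; 0/15 is below it.
- Over both arms: 2/30 = 6.7% is above 5%; 1/30 = 3.3% is below it.

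Leaving out one subject who stopped because of discomfort can therefore change the conclusion.

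**7. Cost of not replacing.** For a single two-sample t-test at d = 0.91 (not the plan's four-time-point calculation), power is 67.2% with 15 and 15, 65.6% with 15 and 14, and 64.0% with 14 and 14. The loss is 1.6 or 3.2 points.

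**The case against.** The strongest reply is that the text says dropouts are replaced, not that their data are discarded. Analysis sets are commonly left to an analysis plan, which is not shown. If dropouts stay in their arm and a further subject is newly randomised, the selection bias does not arise. This stands as a limit on the point: removal is the natural reading of the rule, but it is not written. It does not clear the rule, because substitution during conduct is stated in the protocol itself and an analysis set cannot supply an allocation for the added subject.

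Four stronger readings are tempting, and the documents do not support them.

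- **That the rule favours TPS.** The direction is not fixed. Losing poorly responding sham subjects would bias against TPS, and equal loss in both arms would cancel. Participants and parents are blinded, and sham is described as giving similar sounds and stimuli.
- **That a replacement goes into the vacated arm, known in advance to the person who interviews candidates.** The principal investigator both interviews candidates and delivers treatment, and the interventionist is not listed among those blinded. But the text does not say that the vacated arm is filled, allocation is off-site, and the minimisation program could allocate a 31st subject.
- **That replacement contradicts multiple imputation.** The two can coexist: imputation still serves missing scores at the 1- and 3-month visits and gaps in subjects who stay.
- **That discomfort in dropouts goes uncounted.** The safety section provides for monitoring adverse events at every session, and nothing says these records are dropped.

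**Conclusion.** The point holds in moderate form and should be fixed. The protocol states a rule that, on its natural reading, substitutes randomised subjects after treatment has started. Its described block scheme ends at exactly 30 allocations, with no stated route for a replacement.

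The bias may run either way and depends on two conditions that the documents do not settle: that replaced subjects leave the analysis, and that dropout is outcome-related and differs by arm. Under deliberately unfavourable assumptions, one replacement is worth about 0.12 SD and takes false significance favouring TPS from about 2.4% to 5.5%. Under the milder assumptions it is about 0.05 SD and 3.4%. Both shifts are small beside the planned 0.91 SD, so the rule could not by itself create an effect of the planned size. The discomfort conclusion is more fragile, since it can turn on one subject if dropouts are not counted.

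**What to change.** Delete the replacement sentence, or state that any added subject is newly randomised by a described procedure and does not displace the dropout. In either case:

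- analyse every randomised subject in the assigned arm;
- keep collecting T2 to T4 assessments from those who stop TPS;
- handle scores still missing with the mixed model and multiple imputation already planned;
- count every subject who received at least one session in the discomfort rate.

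The change is mainly one of wording, plus outcome collection after TPS is stopped. At the stated attrition it costs one or two complete cases, with the small loss of power shown above. The Trial status section gives recruitment as 1 June to 30 September 2022. If a replacement has already been made, the analysis and counting rules can still be applied and the replacement reported.
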